**Randomisation**

Memantine group

Placebo group

Week 1: 5mg once daily (+ placebo) (1 tablet twice a day)

(1 tablet twice daily)

Week 1: 1 tablet twice a day

Week 2: 5mg twice a day

10 mg nocte

(1 tablet BD)

Week 2: 1 tablet twice a day

Week 3: 5mg in the morning and 10mg in the evening

Week 3: one tablet twice a day

1 tablet BD

Week 4 – 10mg twice a day then continue

Week 4 – one tablet twice a day then continue

If patient responding and with no adverse effects, **continue** with this regime. If no improvement or a worsening in agitation occurs use rescue protocol if first 3 weeks if non effective or after 3 weeks then stop imp and use trust policy guidelines for BPSD according to clinical need.

12 weeks – This is an acute study and no data on long term effects on agitation, patients will stop treatment.

- - 1. **Intervention and control**

Patients randomised to the active drug arm will be prescribed active memantine. All the tablets supplied will be 5mg and 10 mg size. The dose regime will be as follows; week 1: 5mg in the morning-due to packaging for active Memantine arm this is will be placebo am and Memantine 5mg pm-Those on placebo arm will be 1 placebo twice daily ; week 2: 5mg twice daily; week 3: 5mg in the morning and 10 mg in the evening; week 4: 10mg twice daily.

Patients randomised to the placebo arm will receive placebo memantine. This will be identical in form (tablet size, shape and packaging) to the active drug. The titration regime will be as for the active drug.

If a serious worsening in agitation occurs, by clinical assessment the patient will be offered rescue therapy if this occurs during dose titration stage i.e. first 3 weeks (see appendix 5 for details of rescue therapy). If the serious worsening occurs after the titration phase or rescue therapy fails to work (if the patient is in the first 3 weeks of the study) the patient will be unblinded if appropriate. The patient will then be offered medication if appropriate by their consultant at a dose titrated according to clinical need and/or trust BPSD protocol (appendix 6). If worsening is attributed to memantine then the consultant will be advised to utilise the trust BPSD protocol.

Patients who have completed the trial will have trial medication stopped. Should agitation return then primary care/ local Community Mental Health Teams will treat as per standard practice for example as per trust guidelines- appendix 6.

Onward prescription is not justifiable: (1) as there is no evidence of long term benefit of the medication, (2) Agitation is commonly transient/ acute and the trial rationale is to contain this until the behaviour has passed- in other words an acute phase study, (3) as a result of blinding for duration of study it will not be known if patients were on active or placebo hence giving memantine may not be efficacious and the trial is to answer this question and (4) new onset intercurrent non psychotropic medication responsive causes may be relevant for example delirium.

- - 1. **Rescue Protocol**

To maximise retention in the trial the rescue protocol (Appendix 5) will be implemented during the Memantine titration period. If at all possible non-medication approaches will be adopted first. Medication will be used if it is felt that the patient or caregivers safety is compromised. The researcher/CSO will provide some baseline training to the site where patients are recruited. The protocol is derived from best practice in UK and US, existing studies e.g. CALM-AD and a consensus of all TSG members.

- - 1. **Trial Material & Supply**

Memantine as listed in BNF (section 4.11):

Ebixa® (Lundbeck) will be supplied in wallet packs of 5mg and 10mg tablets.

- - 1. **Dispensing Procedure**

Patients will take varying numbers of tablets according to instruction on dispensed medication packs .

The medication will be dispensed by the Oxleas NHS Foundation trust and East Kent Hospitals Trust Pharmacies and Oxfordshire & Buckinghamshire Mental Health Foundation NHS Trust Pharmacy. Drug receipt will be recorded in the pharmacy study file. The research doctor/CSO will deliver the drugs to the participants in the community in inpatients medication will be provided in standard way. The research doctor/CSO will contact pharmacy to inform them.

- - 1. **Unused Medication & Accountability**

Any unused drug will be disposed of by the research doctor/CSO in line with trust waste disposal guidelines. The research associate will be responsible for destroyed by the relevant pharmacies under the direction of the Research fellow. Used treatment packs will be returned to the pharmacies. Drug dispensing and returns log, including date dispensed, batch number, expiry date, number of tablets dispensed, drug return date and amount.

- - 1. **Prior and Concomitant Interventions**

Patients who have a history of previous failed treatment with memantine will not be entered. No medication changes should have occurred in the 7 days preceding trial commencement.

No other restrictions are placed on other prior or concomitant interventions. A list of all prior medications (& doses) will be obtained as part of baseline data collection.

- - 1. **Adverse Events**

Adverse Events will be managed by the Principal Investigator and Co-Director in line with the European Commission document ‘Detailed guidance on the collection, verification and presentation of adverse reaction reports arising from clinical trials on medicinal products for human use’ (Revision 1, 26th April 2004; Document ENTR/CT 3; <http://pharmacos.eudra.org/F2/pharmacos/new.htm>).

Serious Adverse Events are defined here as:

1. **Serious Adverse Events** – those which are fatal, life threatening, disabling or require hospitalisation or prolongation of hospitalisation. All deaths whether thought to be related to the trial intervention or not should be reported as serious adverse events.

1. **Unexpected Adverse Events** – those that would not be expected among elderly patients with AD (See known side effects in BNF).

If any patient suffers an event that fulfils these criteria, a Serious Adverse Event Form should be completed and faxed to the Principal Investigator **within 24 hours of the event being known.** The original form should be stored in the Investigator File and a copy placed in the patient’s source notes.

A trial (/annual) serious adverse events report will be compiled by the Principal Investigator and sent to the LREC. Serious Unexpected Adverse Events, in addition, will be reported immediately to the TSC .

Expedited reporting is required for all suspected adverse reactions that are both serious and unexpected. Fatal or life-threatening SUSARs should be reported to the LREC and the MHRA as soon as possible but no later than 7 calendar days after the sponsor has knowledge of the minimum criteria for expedited reporting. All other SUSARs and safety issues should be reported to the LREC and the MHRA as soon as possible but no later than 15 calendar days after the sponsor has first knowledge of the minimum criteria for expedited reporting.

Expedited reporting is not required for reactions which are serious but expected and for non-serious adverse reactions whether expected or not. Non-serious adverse events should be recorded using the Adverse Event Form.

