**Protocol Authorisation:**

**Chief Investigator**: **[name]: _________**

**Sponsor Representative [name] ___________________________ Date: _________**

**Trial Director-[name] ________________________________ Date: _________**

**Independent Chair-[name]: _________**

**Trial Synopsis**

| **Name of Sponsor** | East Kent Hospitals University NHS FoundationTrust |
| --- | --- |
| **Title of the Study** | A randomised, double-blind placebo-controlled trial of Memantine in the treatment of the Agitation in Alzheimer’s Dementia |
| **Trial Acronym** | MAGD – Memantine for AGitation in Dementia |
| **Investigators** | [name] (Principal Investigator); [name], [name] , [name], [name], [name], [name], [name], [name] |
| **Study Centre(s)** | Kent and Medway NHS and Social Care Partnership Trust, Oxleas NHS Foundation trust; Peterborough, Berkshire NHS Mental HealthFoundation trust, Oxford and Buckinghamshire NHS foundation trust; Plymouth |
| **Study Period** | September 2007 to May 2010 |
| **Objectives** | **Primary Objectives:** To determine the efficacy of Memantine in the treatment of acute agitation in Alzheimer’s Dementia.  **Secondary Objectives:** To estimate the overall symptom response rate to Memantine in the trial population. To investigate whether there are any adverse effects of Memantine in this population. |
| **Methodology** | A 6 week placebo controlled RCT of Memantine in AD with a blind extension to 12 weeks . Planned enrolment is 164. Patients and their clinician’s may withdraw from the study because of a clinically significant worsening in their psychiatric symptoms. These cases and those remaining under double-blind conditions will be followed for a total of 12 weeks. This will enable us to i)maximise the safety data on Memantine and ii)facilitate recruitment into the study, while retaining a strict 12 week RCT. |
| **Number of participants** | 164 |

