During the study patients will be allowed to continue taking stable doses of concomitant medicines including antidepressants, antihypertensives, anti-inflammatory drugs, atypical anti-psychotics, anticoagulants, laxatives, diuretics, hypnotics and benzodiazepines (Tariot et al, 2004). Concomitant administration of anti-parkinsonian medication will be permitted but stable dose and no patients on amantadine this is to avoid difficulties with PD stability as Memantine can have benefit in PD. Cholinesterase inhibitors will not be permitted unless patients have been stable on that medication for at least 3 months. The commencement of new psychotropic medications will not be permitted during the study except for rescue treatment as per guidelines (appendix 6) for managing the behavioural symptoms of dementia.

- - 1. **Consent / Assent**

The patient or patient’s legally authorized representative must provides written informed consent (with the patients assent) to participate in the trial

- - 1. **Subject Identification**

Patients assessed for eligibility (*prior to consent / assent for participation in the trial*) will be assigned an **identification number.**

Once randomised into the trial (*post consent / assent for participation into the trial*) a subject will be assigned a **randomisation code.**

- - 1. **Stopping Rules** There are two criteria for removal of subjects from the trial;

1. Unblinding will occur in the event of life-threatening change in physical state or need for urgent medical and/or psychiatric intervention as requested by the patient’s treating physician in consultation with the study team and study monitoring committee.

2. Drop out from the 12 week-phase of the study is permitted due to intolerable side-effects and clinically significant persistent uncontrolled agitation. This will be a primary end point but will not necessitate un-blinding for that patient.

If patients withdraw their consent for follow-up then, if at all possible, the reason for loss to follow-up should be ascertained and permission should be requested to use data collected already for the purposes of the trial. No further data will be collected on patients who withdraw from follow-up. They have the right not to give a reason for withdrawing from follow-up and also to request that no data is held on them.

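### Flowchart 6.5.1 stops study drug after week 3 for lack of improvement, while section 6.5.2 acts only on serious worsening or failed rescue, so an unchanged patient is handled in opposite ways before the 6-week primary endpoint

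*Protocol*

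**What the plan says.** Section 6.5.1 (Flowchart) makes continuation conditional: "If patient responding and with no adverse effects", the regimen goes on. For the remaining patients it says "If no improvement or a worsening in agitation occurs use rescue protocol if first 3 weeks", followed by "if non effective or after 3 weeks then stop imp and use trust policy guidelines for BPSD".

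Section 6.5.2 (Intervention and control) uses a different trigger: "If a serious worsening in agitation occurs, by clinical assessment the patient will be offered rescue therapy", limited to the titration stage. It continues with "If the serious worsening occurs after the titration phase or rescue therapy fails to work". The action then is unblinding if appropriate, and medication chosen by the consultant if appropriate. It does not say in words that study drug stops, and it does not mention a patient who is merely unchanged.

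Other places use further wordings:

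- Synopsis, Methodology: patients and clinicians may withdraw "because of a clinically significant worsening in their psychiatric symptoms".
- Synopsis, Duration of Intervention: up to 12 weeks, with adverse effects or worsening agitation as the only exceptions.
- Synopsis, Intervention: repeats the flowchart's condition of continuing if responding, but states no consequence of not responding.
- Section 6.1, design diagram: refers to a deteriorating patient.
- Section 6.2.5 (Stopping Rules): permits drop-out from the 12-week phase for "intolerable side-effects and clinically significant persistent uncontrolled agitation".
- Appendix 5: activates rescue when behaviour deteriorates in the first 3 weeks.

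The synopsis sets the primary endpoint as CMAI change at 6 weeks on 10 mg twice daily. The titration reaches that dose in week 4.

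**The concern.** The flowchart and section 6.5.2 follow one another and are both instructions to sites. They differ on whether an unchanged patient stays on study drug, which is a question many patients in an agitation trial will raise. A site could follow either without knowingly departing from the protocol.

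Two outcomes are exposed. First, the 6-week CMAI comparison: a patient stopped between weeks 3 and 6 is measured off study drug and possibly on other psychotropics under the trust guideline. The stop is prompted by the very behaviour that the CMAI scores, so it is not random with respect to outcome. If memantine works, patients on placebo would be stopped and switched to other treatment more often, and unimproved memantine patients would lose exposure. Both narrow the difference between groups.

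Second, retention: section 6.2.5 calls drop-out a primary end point, the section on determining response expects more memantine patients to remain in the trial, and the Analysis Plan in section 6.7 proposes survival analysis of remaining in trial. If the trigger for leaving is not fixed, neither is that event.

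This is a rule of trial conduct. An analysis plan written later cannot undo different rules having been applied at different sites.

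**Working it through.** The point is textual. It rests on no figure in the plan, and the sample size of 82 per group plays no part in it. The check is to take each kind of patient through both rules.

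**After week 3**

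| Patient's agitation | Flowchart 6.5.1 | Section 6.5.2 |
|---|---|---|
| Improved, no adverse effects | Continue | No trigger |
| Unchanged | Stop study drug, trust guideline | No trigger |
| Worse, but not seriously | Stop study drug, trust guideline | No trigger |
| Seriously worse | Stop study drug, trust guideline | Unblind if appropriate, other medication if appropriate; stopping implied, not stated |

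The two rules agree in the first row and roughly in the last. They conflict in the two middle rows.

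**First 3 weeks.** The flowchart sends unchanged and mildly worse patients to the rescue protocol, and stops study drug if rescue is not effective. Section 6.5.2 offers rescue only for serious worsening. The immediate drug consequence is limited, because Appendix 5 puts psychological approaches first and keeps medication for behaviour that affects safety. The substantive difference is the stopping of study drug.

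**Is the flowchart being misread?** Its sentence is poorly punctuated. The clause before it, however, continues treatment only for responders, and that fits the reading that non-responders stop.

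**Do other sections settle it?** No. The two synopsis exceptions, the design diagram and Appendix 5 each need some deterioration. Section 6.2.5 needs uncontrolled agitation. Since every patient enters with agitation needing treatment (section 6.2.1), some unchanged patients might be brought under 6.2.5. But it is permissive, and it concerns drop-out rather than an instruction to stop study drug. The flowchart alone names lack of improvement as a reason to act.

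**Timing.** Visits fall at weeks 2, 4, 6 and 12. The stop rule applies once week 3 has passed, the full dose starts in week 4, and the primary endpoint is at week 6. The window in which the two rules diverge therefore includes the weeks at full dose before the primary measurement. The flowchart fixes no visit at which non-improvement is judged.

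**Size.** The documents give no rate of non-improvement by week 3 or week 6, and no rate of stopping under either rule. The extra stopping caused by the flowchart rule, and the loss of contrast that follows, cannot be derived from them.

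**The case against.** The best defence is that one badly punctuated flowchart sentence stands against several texts that all require worsening or uncontrolled agitation, and that sites would follow the majority. It also ends by deferring to clinical need. This is fair as a guess about practice. But the flowchart is a stated instruction in the treatment section, and the synopsis repeats its condition for continuing. That sites would in fact diverge is not shown; that the protocol lets them is.

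Three stronger readings are tempting and go beyond the documents.

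- **A stated loss of power.** A reader might assume that 40% stop at about week 4 and lose the whole 6-point effect, giving 6 × (1 − 0.4) = 3.6 points. Scaling from a nominal 80% power, Φ(2.80 × 3.6/6 − 1.96) ≈ 39%. Both inputs are invented. The comparison is with no stopping at all, although section 6.5.2 would also lead some patients to stop. And 39% applies only to a comparison at week 6 alone. Section 6.7.5 analyses the mean of the post-randomisation scores. With a constant effect and equal visit weights, the same assumptions give (6 + 6 + 3.6)/3 = 5.2 points and about 68% over weeks 2, 4 and 6, or (6 + 6 + 3.6 + 3.6)/4 = 4.8 points and about 61% with week 12 added. None of these is an estimate for this trial.
- **Patients removed just as they reach full dose.** The flowchart fixes no decision visit, so the judgement could also fall at week 6 or later.
- **Stopped patients become carried-forward scores.** The synopsis says withdrawn cases will be followed for the full 12 weeks, and section 6.2.5 ends data collection only when consent to follow-up is withdrawn. A stopped patient may well have an observed 6-week CMAI.

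It is also true that section 6.5.2 only implies stopping and that 6.2.5 deals with drop-out. This weakens any claim of two parallel stopping rules. It leaves in place the conflict over the unchanged patient, and adds one more matter to settle.

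**Conclusion.** The protocol is wrong as written: it is internally inconsistent on when study drug stops. After week 3 an unchanged patient, or one mildly worse, comes off study drug under the flowchart and meets no trigger in section 6.5.2. The flowchart is the outlier among the protocol's wordings, which does not by itself show which rule is right.

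The rule applied between weeks 3 and 6 affects who is on study drug or other psychotropics at the primary endpoint, and who counts as remaining in trial. The direction is towards a diluted contrast, assuming that memantine has an effect and that stopping removes some of it. The size is unknown, because no rate of non-improvement is given. Confidence is high for the conflict in wording; no numerical loss of power is claimed.

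**What to change.** Reconcile flowchart 6.5.1, section 6.5.2, section 6.2.5, the synopsis (Methodology, Intervention and Duration rows), the section 6.1 design diagram and Appendix 5, so that there is one trigger for rescue and one for stopping study drug, worded identically in each place. State explicitly what happens to a patient who is unchanged, and whether study drug stops when the section 6.5.2 trigger is met. The clinical team chooses the triggers; the statistical requirement is only that there be one of each.

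The cost is a wording amendment and its notification to sites. It needs no extra patients, visits or assessments.

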If there is a deteriorating patient;

-Withdraw (without breaking blind)

-or treat clinically rescue alternatives up to week 3 of trial only

Study Group

Rescue Group

Placebo Group

12 week assessment

4 week assessment

- 1. **Selection & Withdrawal of Study Population**

To be eligible for entry into the trial individuals must satisfy **all** of the inclusion criteria and **none** of the exclusion criteria.

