**Randomisation**

- - 1. **Recruitment Strategy**

We will employ a full time research doctor of post MRCPsych status. They will be involved in publicising the trial and maintaining awareness but the main role will be recruiting and following up patients. CSOs will be trained in assessing capacity with the purpose of consenting for participation in the trial, obtaining consent and undertaking the assessments. The screening will be supervised by a doctor who will also complete physical examination, review blood test results, complete Hachinski score, the diagnosis of probable dementia and the staging.

We will recruit from primary care and secondary care inpatients as well as direct from care homes. The research worker will assess the patient and meet with the family. We will recruit those patient who have a diagnosis of probable Alzheimers and clinically significant agitation as per inclusion criteria. The research doctor/CSO will liaise with primary care. There will also be site training on the rescue protocol and primary care will also be made available of the rescue protocol.

Eligible patients will be recruited from the Older Persons Mental Health inpatient Units at William Harvey Hospital Ashford and St Martins Hospital Canterbury—There are 116 beds in the trust. We will also have access to a further 184 beds from the West Kent trust if needed for recruitment. Our initial plan is to focus on 2 sites William Harvey and St Martins which have 90 beds in total. We will also recruit from 24 hour residential facilities in the region. We have good links already with care homes.

The Oxleas NHS trust site will recruit patients form inpatient wards (56 beds), nursing and residential homes where we have established partnerships with such institutions. There are around 2500 residential and nursing homes in the Oxleas district with some 300 + dementia nursing beds.  We will also be open to recruitment from community dwelling patients,
particularly those in receipt of the Oxleas home care for advanced dementia.

The Oxford site covers Oxfordshire, Berkshire, Buckinghamshire and South Northamptonshire. Recruitment will focus on the 3829 care home beds in Oxford and 3545 in Buckinghamshire (not including Milton Keynes). Patients will also be identified through the Deeparc System.

Peterborough and Plymouth site will use similar recruitment.

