Patients will be allocated to one of the two trial arms (ratio 1:1). Once informed consent or assent has been given, baseline assessment completed , the research fellow/CSO will obtain a treatment code for the subject. Patients will be assigned codes consecutively as they enter the trial. The codes will correspond to the pre-randomised medication packs provided by Lundbeck. There will be a sealed envelope for each treatment code containing details of whether the medication pack for that code contains active drug or placebo. Balancing for severity of agitation, staging of dementia and smoking status will be included. Randomisation using the minimisation approach will ensure that equal numbers are entered into each arm of the trial. Patients will be registered for the trial using an internet allocation system.

- - 1. **Blinding & Unblinding**

It is important that blinding is maintained throughout the trial until the database is closed and the data analyses have been performed.

Unblinding will occur in the event of life-threatening change in physical state or need for urgent medical and/or psychiatric intervention as requested by the patient’s treating physician in consultation with the study team and study monitoring committee.

Unblinding in such circumstances will only occur if it is felt that knowledge of the patients medication status will impact on future medical care.

If unblinding occurs accidentally, it is important that the unblinded individual completes an Accidental Codebreak Form (see Appendix4) for each instance of unblinding (copies will be available from the Trial Research Fellow/CSO).

- 1. **Trial Interventions**
     1. **Flowchart**

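### Section 6.5.2 allows unblinding when agitation seriously worsens, against the design chart and without citing the 6.4.3 test, so some later CMAI ratings could be made unblinded

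*Protocol*

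**What the plan says.** The protocol deals with a deteriorating patient, and with breaking the code, in several places.

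- **Section 6.5.2 (Intervention and control).** One rule covers serious worsening past titration and failed rescue alike: "rescue therapy fails to work (if the patient is in the first 3 weeks of the study) the patient will be unblinded if appropriate". Treatment by the consultant then follows clinical need and/or the trust BPSD protocol. If the worsening is attributed to memantine, the advice is again the trust protocol.
- **Section 6.1 (design chart).** A deteriorating patient is to be handled thus: "Withdraw (without breaking blind", or given rescue treatment up to week 3 only.
- **Section 6.5.1 (flowchart).** If rescue is ineffective, or "after 3 weeks then stop imp and use trust policy guidelines for BPSD according to clinical need". It does not mention the code.
- **Section 6.2.5 (Stopping Rules).** On drop-out for intolerable side effects or persistent uncontrolled agitation: "This will be a primary end point but will not necessitate un-blinding for that patient".
- **Section 6.4.3 (Blinding & Unblinding).** The trigger is a life-threatening physical change or an urgent medical or psychiatric need, at the request of the "treating physician in consultation with the study team and study monitoring committee". It adds: "Unblinding in such circumstances will only occur if it is felt that knowledge of the patients medication status will impact on future medical care".
- **Section 6.6 (Unblinding Reporting).** The person who has been unblinded completes a Codebreak Form, which is faxed to the Chief Investigator. The original is kept locked away.

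**The concern.** Section 6.5.2 ties a possible code break to worsening agitation, which is what the CMAI measures. It gives no criterion of its own, names no decision-maker and does not point to 6.4.3. A site working from 6.5.2 alone could break the code more readily than 6.4.3 intends, in patients selected by how they are doing on the primary outcome.

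The CMAI is rated by a researcher who draws on staff and relatives, so knowing the allocation can colour the score. If patients are still rated after a break, some of those ratings may not be blind. Worsening after week 3 can come before the week-6 rating on which the primary endpoint rests.

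**Working it through.** No arithmetic decides this point; it rests on comparing the sections.

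**1. Do the rules for a deteriorating patient agree?**

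| Section | Patient | Code |
|---|---|---|
| 6.1 chart | Deteriorating | Withdraw, blind kept |
| 6.5.1 flowchart | No improvement or worse; rescue ineffective or past week 3 | Silent; stop drug, trust guidelines |
| 6.2.5, second rule | Drop-out for uncontrolled agitation | Unblinding not required, not forbidden |
| 6.5.2 | Serious worsening after titration, or failed rescue | Unblinding if judged appropriate |
| 6.4.3 | Life-threatening change or urgent need | Only if the allocation will affect care |

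The direct conflict is between 6.5.2 and the 6.1 chart. Section 6.2.5 is compatible with either, and 6.5.1 takes no position.

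**2. Does the care that follows need the allocation?** Sections 6.5.1 and 6.5.2 both lead to treatment by clinical need or the trust protocol. Neither makes that care depend on the arm. The later argument in 6.5.2 against onward prescription also assumes that the arm stays unknown for the duration of the study.

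**3. Are these patients rated afterwards?** The Synopsis (Methodology) follows patients withdrawn for worsening for a total of 12 weeks. Section 6.6 schedules CMAI for each patient at weeks 2, 4, 6 and 12, which is 4 post-baseline ratings. Counting the scheduled ratings that fall after a break:

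- before week 2: weeks 2, 4, 6 and 12, so 4 of 4;
- between weeks 2 and 4: weeks 4, 6 and 12, so 3 of 4;
- between weeks 4 and 6: weeks 6 and 12, so 2 of 4;
- after week 6: week 12 only, so 1 of 4.

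Any break before week 6 precedes the week-6 rating. These are counts from the visit schedule, not estimates of how many ratings would be unblinded. Section 6.2.5 lists unblinding among its two criteria for removal from the trial, so a code-broken patient may not be rated again.

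**4. Is the rater kept apart from the allocation?** Section 6.3.2 says: "CSOs will be trained in assessing capacity with the purpose of consenting for participation in the trial, obtaining consent and undertaking the assessments". Under Baseline Assessments (section 6.3), the research doctor or CSO examines the notes and speaks to the key nurse and, if possible, the relative. Later ratings use the same caregiver where possible. Section 7.1 places the follow-up assessment forms and the unblinding log together in the source notes. The locked Codebreak Form in 6.6 gives some protection, but no section says that the rater or informant stays blind once the code is broken.

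**The case against.** The strongest reply is that 6.4.3 already governs. It is the section on blinding, it comes just before 6.5, and its trigger includes urgent psychiatric need, which serious worsening may well meet. On that reading 6.5.2 lacks only a cross-reference. This is a fair reading and it limits the weight of the point. It does not remove the conflict with the chart, and 6.5.2 does not itself state the reading.

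Four stronger inferences are tempting, and the documents do not support them.

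- *That worsening requires unblinding.* Section 6.5.2 is permissive.
- *That the protocol contradicts itself throughout.* Only the 6.1 chart is in direct conflict with 6.5.2.
- *That raters learn the allocation.* Consulting the study team about a break is not telling it the result. Section 6.4.3 says of the Accidental Codebreak Form that "copies will be available from the Trial Research Fellow/CSO", but handing out a blank form reveals nothing, and that form concerns accidental breaks. The log in 7.1 is not said to record the arm.
- *That the bias can be sized.* This would need the share of patients code-broken and still rated, and the shift in their scores. The protocol gives neither. The planned 20% attrition in 6.7.2 is an allowance for patients lost, so it cannot stand in for patients who are still rated.

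It can also be said that if code-broken patients are removed, LOCF would supply week 6 from an earlier rating, made before the break. That is possible. The protocol does not settle which course applies.

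**Conclusion.** The point holds as a conflict in the rules for conduct that leaves the primary outcome open to avoidable bias. Sections 6.5.2 and 6.1 give different instructions for overlapping patients, and 6.5.2 does not refer to the narrower test in 6.4.3. Some CMAI ratings after a break, including week 6, could be made unblinded.

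This rests on two conditions that the protocol leaves open: that some code-broken patients continue to be rated, and that the allocation reaches the rater or informant. The frequency is unknown and no size of bias can be derived. The point does not belong to the statistical analysis plan, because who may break the code and who learns the arm are matters of conduct, and no analysis can re-blind a rating. It should be corrected because the wording is easily changed and emergency unblinding stays available.

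**What to change.** In section 6.5.2, replace the permission to unblind with: *study drug is stopped and the patient is treated per trust protocol with the blind kept; the code is broken only if the test in 6.4.3 is met.* This brings 6.5.2 into line with the 6.1 chart and the 6.5.1 flowchart.

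In section 6.4.3, add: *the allocation is disclosed only to the treating physician; it is not disclosed to the CMAI rater and is not recorded in the source-note log.* The log can still record that a break took place.

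The cost is amendment wording and one filing rule: the record of the allocation must be kept apart from the source notes. Section 6.6 already locks away the original Codebreak Form, so the arrangement is not new. Emergency access to the code under 6.4.3 is unchanged.
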